# Clinical effectiveness, quality of life and cost-effectiveness of Flaminal® versus Flamazine® in the treatment of partial thickness burns: study protocol for a randomized controlled trial

**DOI:** 10.1186/s13063-016-1240-5

**Published:** 2016-03-05

**Keywords:** Flaminal®, Silver sulfadiazine, SSD, Flamazine®, Partial thickness burns, Burns

## Abstract

**Background:**

Partial thickness burns are painful, difficult to manage and can have a negative effect on quality of life through scarring, permanent disfigurement and loss of function. The aim of burn treatment in partial thickness burns is to save lives, stimulate wound healing by creating an optimumly moist wound environment, to have debriding and analgesic effects, protect the wound from infection and be convenient for the patient and caregivers. However, there is no consensus on the optimal treatment of partial thickness wounds. Flaminal**®** and Flamazine**®** are two standard treatment options that provide the above mentioned properties in burn treatment. Nevertheless, no randomized controlled study has yet compared these two common treatment modalities in partial thickness burns. Thus, the aim of this study is to evaluate the clinical effectiveness, quality of life and cost-effectiveness of Flaminal**®** versus Flamazine**®** in the treatment of partial thickness burns.

**Methods/Design:**

In this two-arm open multi-center randomized controlled trial, 90 patients will be randomized between Flaminal**®** and Flamazine**®** and followed for 12 months. The study population will consist of competent or temporarily non-competent (because of sedation and/or intubation) patients, 18 years of age or older, with acute partial thickness burns and a total body surface area (TBSA) of less than 30 %. The main study outcome is time to complete re-epithelialization (greater than 95 %). Secondary outcome measures include need for grafting, wound colonization/infection, number of dressing changes, pain and anxiety, scar formation, health-related quality of life (HRQoL), and costs.

**Discussion:**

This study will contribute to the optimal treatment of patients with partial thickness burn wounds and will provide evidence on the (cost-)effectiveness and quality of life of Flaminal**®** versus Flamazine**®** in the treatment of partial thickness burns.

**Trial registration:**

Netherlands Trial Register NTR4486, registered on 2 April 2014.

## Background

Partial thickness burn wounds are painful, difficult to manage, and susceptible to infection [1]. The aim of burn treatment in partial thickness burns is to promote rapid wound healing, decrease pain and suffering, protect the wound from infection, minimize scar formation and functional impairment, and to enable patients to return to normal daily activities as soon as possible [2, 3]. Thus, an ideal dressing should stimulate wound healing by creating an optimumly moist wound environment, but also have a debriding and analgesic effect. Moreover, an ideal dressing should protect the wound from infection and be convenient for the patient and caregivers.

Nowadays, many topical dressing materials are available for the treatment of superficial and deep partial thickness burns, while there is no strong evidence to support their use [4]. In clinical practice, silver-containing dressings and topicals, in particular silver sulfadiazine (SSD), have been the most commonly used burn wound dressing in the treatment of partial thickness burns for over 30 years [4–8].

The popularity of SSD can mainly be explained by its antimicrobial effect in vitro against a wide range of gram-positive and gram-negative microorganisms including resistant forms such as methicillin-resistant *Staphylococcus aureus* (MRSA) and vancomycin-resistant *Enterococcus* (VRE), and against fungi and anaerobes [9–11]. However, a Cochrane review of 26 randomized controlled trials (RCTs) found insufficient evidence to establish whether silver-containing dressings or topical agents prevent wound infection more effectively compared to non-silver containing treatments [12].

Several studies have shown that silver is highly toxic to both keratinocytes and fibroblasts in in vitro models [7, 13–15]. Other studies found that SSD will form a pseudoeschar which can promote bacterial proliferation and requires frequent removal or debridement on a daily basis to facilitate re-epithelialization and the optimal assessment of the wound state. In contrast, two other studies found that some silver preparations are not toxic and suggest positive effects of silver on wound healing [16, 17]. A number of systematic reviews of clinical trials showed that SDD is consistently associated with poorer wound healing than non-silver treatment for superficial and partial thickness burns [4, 18, 19]. However, the results of these reviews should be interpreted with caution because of the high risk of bias in these clinical trials. With regard to costs, a number of studies suggested that SDD is less cost-effective than Mepilex® Ag, Aquacel® Ag and Acticoat® [20–24].

Recently, Flaminal® (Flen Pharma, Kontich, Belgium) was introduced onto the market. Flaminal® consists of hydrated alginates polymers in a polyethyleneglycol (PEG) matrix embedded with a biologic enzyme system based on glucose oxidase and lactoperoxidase that are stabilized by guaiacol [15]. This enzyme system forms free radicals which destroy the cell wall of absorbed bacteria. Furthermore, short-chain PEG dissolves dry scab and necrotic material which results in lysed material. Wound exudate, including bacteria, and lysed material is absorbed by alginates in hydrated form. These two steps result in continuous debridement [25, 26].

Pre-clinical data by Vandenbulcke et al. and de Smet et al. showed that Flaminal® Forte is not toxic to keratinocytes and fibroblasts in vitro [15, 27]. In effect, Flaminal® Forte may not damage skin cells which will finally result in undelayed wound healing. Two studies have indicated a faster wound healing when a partial thickness burn wound was treated with Flaminal® Forte compared to SSD [28, 29]. But these results should be interpreted with caution due to the retrospective design of these studies. However, a shorter wound healing time would not only reduce length of hospital stay (LOS) but probably also scar formation since Deitch et al. and Cubison et al. demonstrated that burn wounds which heal within 21 days have less risk of developing hypertrophic scars and contractures [1, 30].

There are studies showing conflicting data with respect to bacterial growth under Flaminal® Forte; with some demonstrating count reductions [15, 27] while others show increases [29].

Dressings with SSD should be changed every 24 hours, and removing the pseudoeschar, which is a result of the SSD base drying out, is usually painful. In contrast, Flaminal® Forte can be applied every other day after the third post-burn day (PBD) and can be removed easily from the wound. However, the effect on pain perception and anxiety during dressing changes between these treatments have not yet been compared. Also, the effect of both treatments on LOS, scarring and health-related quality of life (HRQoL) are not known.

Finally, medical costs including those for medical staff, materials for wound care, surgical procedures, hospital stay, HRQoL, and productivity loss due to the burn injury are unknown for both treatments. A cost-effectiveness analysis is thus mandatory to evaluate the long-term health economic outcomes of the studied treatments and justify the application of both treatments in clinical practice.

### Objectives

The aim of this study is to evaluate the clinical effectiveness, quality of life and cost-effectiveness of Flaminal**®** versus Flamazine**®** (SSD) in the treatment of partial thickness burns.

## Method/Design

This investigator initiated, open label, multi-center, RCT compares the effects of treatment and cost-effectiveness of Flaminal**®** Forte versus Flamazine**®** in the treatment of partial thickens burns.

### Study population

The study will be performed in two of the three burn centers (Beverwijk and Rotterdam) in The Netherlands. In these burn centers, both Flaminal® and Flamazine® are therapeutic options for treating partial thickness burns. Patients who are admitted to the Beverwijk or Rotterdam Burn Centre and who meet the following inclusion criteria will be eligible for this study: competent or temporarily non-competent (because of sedation and/or intubation); partial thickness burns of minimally 1 % total body surface area (TBSA) (possibly in combination with full thickness burns); hospital admission within 48 hours of burn injury; written informed consent by the patient. Patients meeting one or more of the following criteria are excluded: age below 18 years; TBSA of more than 30 %; burns caused by chemicals, electricity or radiation; if local therapy with a topical agent has already started; patients who are expected (according to the treating medical physician) to be non-compliant with the study protocol.

### Recruitment, consent and randomization

All patients who are admitted to the burn center undergo standardized screening and baseline procedures according to the local protocol. The local investigator will check the inclusion and exclusion criteria of the study and will inform the participant about the study. If the participants are willing to participate in this study, they must provide written informed consent. If an eligible patient is temporarily non-competent because of sedation and/or intubation, a legal representative of the patient, according to the Dutch Medical Treatment Act (WGBO), will be informed about the study and will provide written informed consent. After the sedation or intubation has ended, the patient will be asked to confirm willingness to participate in the study in writing, otherwise the participation is discontinued and the collected study data will be destroyed.

After informed consent has been obtained, the largest partial thickness area will be assigned as the study area. Thereafter, the patient will be randomly assigned to one of the two study arms using TenALEA (Trans European Network for Clinical Trials Services), an online randomization program (www.flam-studie.nl). The online-randomization is stratified by center and uses variably sized blocks in a 1:1 ratio. In both participating hospitals the local trial coordinator will receive a username and password for online randomization. After randomization the local trial coordinator of that center and the central trial coordinator will receive an email with the inclusion number and the randomization outcome. The outcome will also be displayed on the website, only visible for the randomizing local and central trial coordinators. Then, all the burn wounds will be treated with the treatment that is assigned by the randomization.

When the study area that was initially assessed as a partial thickness burn, turns out to be a full thickness burn area after performing laser Doppler imaging (LDI), then the study area will be replaced: the second largest partial thickness area (confirmed by LDI) will then be chosen as the study area.

For practical reasons it is not possible to blind the patients. It is also impossible to blind the medical staff who provide the burn wound care, because they are involved in all aspects of the care and are able to recognize each treatment from its appearance. No blinding of other outcomes is also possible for the same reasons.

### Interventions

The patient will be allocated to one of the following treatments:o*Flaminal® Forte:* treatment with Flaminal® Forte (glucose oxidase-lactoperoxidase guaiacol complex of 50 g in 5.5 % alginogel) will be initiated within 24 hours after admission. Before applying Flaminal® Forte on the wound, pain medication must be given. Paracetamol, Oxynorm and Oxycontin will be used as standard pain medication. The usage and doses of pain medication will be monitored. The burn wound will be cleaned and rinsed with Prontosan® followed by careful dabbing and drying of the wound. The wound will then be covered with a non-adhesive dressing on which a sufficiently thick layer (4–5 mm) of Flaminal® Forte has been applied. A net bandage/dressing will be used to keep the dressing in place. Dressing changes will be performed daily during the first 3 days post burn and thereafter every other day. If an infection is suspected, or in case of leaking or insufficient gel, the dressing with Flaminal® Forte may be changed daily after 3 days post burn. In case of wound colonization or infection, treatment with Flaminal® Forte will be changed to another relevant treatment based on the results of the wound cultureo*Flamazine®:* treatment with Flamazine® (silver sulfadiazine 10 mg/g in hydrophilic crème base) will consist of daily washing and application of Flamazine®. Before applying Flamazine® on the wound, pain medication must be given. Paracetamol, Oxynorm and Oxycontin will be used as standard pain medication. The usage and doses of pain medication will be monitored. The burn wound will be cleaned and rinsed with Prontosan® followed by carefully dabbing and drying of the wound. A sufficiently thick layer (at least 2–3 mm) of Flamazine® will be applied directly on the wound. The cream will be covered with a non-adhesive dressing. A net bandage/dressing will be used to keep the dressing in place. This procedure is repeated once every 24 hours until the sixth day post burn. Thereafter, the treatment of all patients in this study arm will consist of Furacine Soluble Dressing (Furacine 2 mg/g ointment) on the seventh day post urn, and Flamazine® on the eighth day post burn. Treatment with Furacine Soluble Dressing and Flamazine® will be alternated until complete wound healing/operation because of the cytotoxicity of the silver particles in Flamazine® on the wound bed when used continuously. In case of wound colonization or infection the treatment will be replaced with another relevant treatment based on the results of the wound culture

After discharge, patients in both group will be treated in an outpatient setting, according to the local protocol.

### Outcome measures

#### Primary outcome

Primary endpoint is time to complete re-epithelialization (greater than 95 %) of the study area, in days, judged by two experienced burn specialists during each dressing change. Complete re-epithelialization of the study area is only affirmed when the two burn specialists agree with each other.

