
**Table 1 Tab1:** Clinical assessment and laser Doppler imaging (LDI) results

Classification	Clinical properties						LDI color
	Blisters	Color/Appearance	Pliability	Capillary refill	Pain	Healing time	
Superficial partial thickness burns	Small blister: intact and open	Pink-red, shiny	Supple	<2 sec	++	Within 14 days	Red
Intermediate partial thickness burns	Blisters: intact and open	Pink-red, shiny and dry	Mix of supple and stiff	<2 sec	+	14–21 days	Yellow
Deep partial thickness burns	Blisters: intact and open	Red, shiny and dry	Mix of supple and stiff	>2 sec	+/-	>21 days or even no spontaneous healing	Blue
Full thickness burns	None	White-yellow, red, brown and black	Stiff	>2 sec	-	No spontaneous healing	Blue

A schedule with baseline and outcome measurements during the study is presented in Table 2.

**Table 2 Tab2:** Time schedule for study procedures and assessments

Procedure/Assessment	Admission	Treatment phase	Follow-up (month)		
			3	6	12
Standard screening, baseline procedures	x				
Check eligibility (inclusion criteria)	x				
Provide patient Information	x				
Obtain written informed consent	x	x (confirmation by patients who were initially non-competent)			
Randomization (Flaminal® vs Flamazine®)	x				
Baseline parameters	x				
LDI		x			
Wound colonization	x	x			
Wound healing		At each dressing change			
Need for surgery of partial and/or full thickness burns and % of study area requiring skin graft		10–14 PBD			
Colonization	x	Swabs on Mondays and Thursdays			
Infection	x	Clinical judgment during dressing changes			
Dressing changes	x				
Use of systemic antibiotics	x				
Pain and anxiety					
Visual analogue thermometer (VAT)	x	Daily, before and after dressing change and in the evening			
Itching	x	Daily in the evening on 7^th^ ±2 PBD and day of discharge			
Burn Specific Pain and Anxiety Score (BSPAS)	x				
Health-related quality of life (HRQoL)		In the last week of hospitalization			
Burn Specific Health Scale Brief (BSHS-Brief)		In the last week of hospitalization	x	x	x
EuroQol-5D (EQ-5D)			x	x	x
Scarring					
POSAS			x	x	x
Cutometry			x	x	x
Dermaspectrometry			x	x	x
Costs		Daily	x	x	x

*LDI* laser Doppler imaging, *PBD* post-burn day

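### Healing is read only at dressing changes, which are daily with Flamazine but every other day with Flaminal after day 3, so an ordinary log-rank test compares unequally delayed healing days

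*Protocol article*

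**What the plan says.** All references are to the protocol article.

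- **Primary outcome.** Time to healing of the study area, in days, is "judged by two experienced burn specialists during each dressing change". The wound-healing row of Table 2 says only "At each dressing change". The Primary outcome section also makes agreement a condition: "Complete re-epithelialization of the study area is only affirmed when the two burn specialists agree with each other".
- **Interventions, Flaminal arm.** "Dressing changes will be performed daily during the first 3 days post burn and thereafter every other day". There is an exception for suspected infection, leakage or too little gel, when "the dressing with Flaminal® Forte may be changed daily after 3 days post burn".
- **Interventions, Flamazine arm.** "This procedure is repeated once every 24 hours until the sixth day post burn". From then on Furacine is used on day 7 and Flamazine on day 8, and the two "will be alternated until complete wound healing/operation". Daily changes after day 6 follow from that alternation but are not stated.
- **Both arms.** Colonization or infection leads to another treatment chosen on the culture result, with no stated dressing frequency. After discharge, patients "will be treated in an outpatient setting, according to the local protocol".
- **Statistical analysis.** Healing times go into Kaplan-Meier curves and a log-rank test. The Cox model is reserved for baseline imbalance.

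**The concern.** The randomized arm sets how often the primary endpoint can be seen. A wound that heals between two inspections is dated to the later one, and that wait is longer where inspections are further apart. An ordinary log-rank test on the recorded day cannot tell the extra wait from slower healing.

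The direction is known: against Flaminal. The distortion can hide part of a real benefit or produce a false deficit. A larger sample does not remove it, and neither does Cox adjustment for baseline covariates. The same healing difference is the denominator of the cost-effectiveness ratio in the Economic evaluation section, so the distortion carries over there.

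**Working it through.** **The plan's own figure.** The article gives no figure for recording delay. Its sample size section states means of 11 and 6 days, SD 7.5, alpha 5%, 80% power and 41 per arm. Taking the test as two-sided (an assumption), n = 2 × [7.5 × (1.960 + 0.842) / 5]² = 35.3, so 36 per arm, or 37 with the t distribution. The stated 41 is larger than these inputs require. It is used below as stated, and the point does not depend on it.

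**Delay per wound.** If healing is equally likely at any moment between inspections L days apart, the mean delay is L/2.

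- Daily: 1/2 = 0.5 day.
- Every other day: 2/2 = 1.0 day.
- Difference: 0.5 day, for wounds healing after day 3 only. Up to day 3 both arms are inspected daily.

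**Average gap over all Flaminal wounds, full adherence.** Gap = P(healing after day 3) × mean gap among those wounds. Gamma healing times are assumed, and strict two-day steps after day 3:

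| Mean, SD (days) | P(after day 3) | Gap among these | Average gap |
|---|---|---|---|
| 6, 7.5 | 0.524 | 0.541 | 0.28 |
| 11, 7.5 | 0.907 | 0.515 | 0.47 |
| 14, 7.5 | 0.982 | 0.505 | 0.50 |

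Lognormal times give 0.33 day at a mean of 6 and 0.49 day at a mean of 11. At the planned Flaminal mean the gap is thus 0.28/5 = 5.6% to 0.33/5 = 6.6% of the planned 5-day difference. If a share f of the later Flaminal changes is in fact daily, the gap among wounds healing after day 3 is about 0.5 × (1 − f).

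**Rough check as a comparison of means.** SE = 7.5 × √(2/41) = 1.656 days.

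- No true difference, 0.5-day shift: 0.5/1.656 = 0.302, so the two-sided error is 1 − Φ(1.960 − 0.302) + Φ(−1.960 − 0.302) = 6.05%. A 0.25-day shift gives 5.3%.
- Design difference reduced from 5 to 5 − 0.3 = 4.7 days: power goes from Φ(5/1.656 − 1.960) = 85.5% to Φ(4.7/1.656 − 1.960) = 81%.

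**Simulation of the planned log-rank test.** 41 per arm, SD 7.5, full adherence, every wound healing, 4,000 trials per scenario:

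| Scenario | Shape | Daily in both arms | Protocol schedules | Common two-day grid |
|---|---|---|---|---|
| 11 vs 11 days, two-sided error | gamma | 4.8% | 7.1% | about 5% |
| 11 vs 6 days, power | gamma | 80% | 72% | 82% |
| 11 vs 6 days, power | lognormal | 92% | 86% | 92% |

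Over both shapes the null error was 7.0 to 7.5%. Results significant against Flaminal made up 6.2 to 6.6%, where 2.5% is nominal. The Monte Carlo standard error at 7.1% is √(0.071 × 0.929/4000) = 0.4 points, and separate runs differ by about a point. With a common grid both error and power recover, so the loss comes from the unequal schedules and not from coarse dating as such.

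**The case against.** The best counter-argument concerns size. Full adherence to the two-day schedule is an assumption. The article allows daily Flaminal changes in some circumstances, lets either treatment be replaced on culture results, and leaves outpatient care to the local protocol, which may treat both arms alike. None of these frequencies is stated. If half of the affected Flaminal assessments were daily (an assumption), false results against Flaminal at SD 7.5 fall to 3.9 to 4.4%, and power at the design difference goes only from 92% to 90% or from 80% to 76%. The bias also runs against the treatment expected to do better, so it mainly makes a positive finding conservative. All of this stands, and it lowers the severity.

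It can also be said that handling of interval censoring belongs in a statistical analysis plan, which is not shown. That is fair for the detail. But the article itself fixes the assessment rule, both schedules and the test, and it is their combination that is biased.

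Stronger readings that a reader might infer, and that the document does not support:

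- *That only the Flaminal arm is recorded late.* Both are; only the difference is at issue.
- *That the gap is 10% of the planned effect.* That sets the half-day, which belongs to a mean of 11 days or more, against a difference that presupposes a Flaminal mean of 6 days.
- *That false results against Flaminal exceed 11%.* Simulation gives this with SD 4, but the article's SD is 7.5.
- *That the two-specialist rule makes it materially worse.* A disagreement could cost two days instead of one, but the article gives no disagreement rate and does not say whether a wound may be re-inspected before the next change.

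**Conclusion.** The point holds in moderate form. As written, the plan dates healing with an arm-dependent delay, and the named test treats that delay as a treatment effect. With full adherence the average gap is about 0.3 day at the planned Flaminal mean and about 0.5 day at a mean of 11 days. At SD 7.5 and 41 per arm this takes the two-sided error from 5% to about 7% and costs about 6 to 8 points of power at 11 versus 6 days.

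These sizes rest on assumed gamma or lognormal times, a strict two-day pattern after day 3, and daily Flamazine-arm changes inferred from the day 7/day 8 alternation. Departures from the two-day pattern shrink the gap. Confidence is high for mechanism and direction and moderate for size. Severity: should-fix.

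**What to change.** Leave both dressing schedules alone and change the analysis wording.

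- **Primary analysis.** Treat each healing time as interval-censored between the actual date of the last assessment not agreed healed and the actual date of the first assessment agreed healed. Apply the same rule to inpatient and outpatient assessments, and compare the arms with a generalized log-rank test for interval-censored data. Choose a likelihood-based score form: a permutation version assumes the intervals are exchangeable between arms, which unequal schedules break.
- **Sensitivity analysis 1.** The ordinary log-rank test on the recorded day.
- **Sensitivity analysis 2.** Both arms coarsened to a common two-day grid, only where the assessment dates allow. Fixed shared days cannot be the main rule, because dressing days become irregular after exceptions, switches and discharge.

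Cost: some extra analysis work and slightly coarser healing times. No new data are needed, provided that the date and judgement of each assessment are on the case record form. The article reports recruitment as complete and data collection planned to end in November 2016, so the wording should be settled before results are compared by arm.
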